|                  | 
again and analysed non-parametrically if normal distribution is missing.
 
Differences between the two groups and test times are calculated for ordinal data as follows: New variables are generated from the difference between the post-intervention and baseline data. The difference between group 1 and 2 is determined using the Mann Whitney-U test. For the ordinal variables FES-I and FOGQ, which are also collected at the follow-up call, a Kruskal Wallis test is performed across all groups and test time points. Changes in fall rate (nominal) between baseline, post-intervention and follow-up will be calculated using Chi-Square test. Metric data will be tested for homogeneity of variance (Levene test) as the basic assumption of a 2 x 2 ANOVA, with "time (baseline, post-intervention)" as the within-factor and "group (1, 2)" as the between-factor. If there is no homogeneity of variance, an alternative F-statistic (e.g. according to Welch or Brown-Forsythe) is used. If the basic assumption of sphericity is not fulfilled, corrected values are used, e.g. according to Greenhouse-Geisser or Huynh-Feldt. To calculate the differences between the groups and measurement times, a 2 x 2 ANOVA (analysis of variance) is performed, followed by pairwise comparisons (Bonferroni correction for all comparisons) between the groups at measurement times 1 and 2 if statistical significance is present. In the case of failure of the adaptive measures, non-parametric tests are used as described for ordinal scaled data. Effect size is reported using partial Eta squared and standardised effect size.
 |
| Timetable | 
Study-related:
 
Recruitment time: 8 months
 
15.04.2021 Planned start: First Patient First Visit (FPFV)
 
15.11.2021 Last Patient First Visit (LPFV)/Last Subject In (LSI)
 
14.12.2021 Planned end: Last Patient Last Visit (LPLV)/Last Subject Out (LSO)
                                                                                                                                                                                                                                                                                                                                                                                                                                                                                                                                                                                                                                                                                                                                                                                                                                                                                                                                                                                                                                                                                                                                                                                                                                                                                                                                                                       |

|  |                                                                                                                                                                                                                                                                                                                                                             |
|--|-------------------------------------------------------------------------------------------------------------------------------------------------------------------------------------------------------------------------------------------------------------------------------------------------------------------------------------------------------------|
|  | 
Patient-related:
 
Active intervention duration: 4 weeks
 
After inclusion, the duration of each participant's participation corresponds to 8 weeks (baseline survey, 4-week intervention, post-intervention testing, focus group only for participants in intervention group 1, follow-up call 4 weeks after end of intervention).
 |
|--|-------------------------------------------------------------------------------------------------------------------------------------------------------------------------------------------------------------------------------------------------------------------------------------------------------------------------------------------------------------|

|                      |                                                                                                                                                                                                                                                                                                                                        |
|----------------------|----------------------------------------------------------------------------------------------------------------------------------------------------------------------------------------------------------------------------------------------------------------------------------------------------------------------------------------|
| Funding       | This clinical study is a self-funded, academic study of the Reha Zentrum Münster, [REDACTED], [REDACTED].                                                                                                                                                                                                                              |
| GCP Statement | The study was planned in accordance with the requirements of the Tyrolean Hospitals Act (Tir KAG), the Declaration of Helsinki and the ICH-E6 guidelines, the OeAWI guidelines for good scientific practice, as well as the requirements of the General Data Protection Regulation (DSGVO) and the Austrian Data Protection Act (DSG). |

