| DRKS ID                | As soon as the Ethics Committee has given its approval, registration in the DRKS or another primary registry is applied for in accordance with the WHO criteria.                                                                                                                                                                                                                                                                                                                                                                                                                                                                                                                                  |
| Study objective        | The study objective is to investigate the effects of an activity-based physiotherapy training programme with eye movement training compared to an activity-based physiotherapy training programme without eye movement training on dynamic balance, mobility with and without multi-task, static and dynamic balance walking speed, health-related quality of life, freezing of gait, fall-associated self-efficacy, depression and fall rate. The aim is also to explore the change in eye movements (saccade velocity, amplitude, latency, fixation duration) over the intervention period and to evaluate the feasibility of a larger randomised controlled trial using predefined parameters. |
| Primary endpoints      | 1.1 Dynamic balance measured by the Functional Gait Assessment (FGA)

1.2 Items 5, 6 and 10 of the FGA are additionally performed with eye-tracking glasses (Tobii Pro Glasses 3) for mobile measurement of eye movements (saccade velocity, amplitude, latency, fixation duration).                                                                                                                                                                                                                                                                                                                                                                                                        |

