### 2.3 Study objectives

Thus, four **study objectives** are pursued to deepen the knowledge on effectiveness:

1. Assessment of the effects on dynamic balance (primary endpoint)
2. Investigating the feasibility of a larger randomised controlled trial
3. assessment of the effects on functional mobility with and without manual multi-task, static and dynamic balance, walking speed, health-related quality of life, freezing of gait, fall-associated self-efficacy, depression and fall rate (secondary endpoints).

4. evaluation of the change in eye movements during the intervention, measured once a week in the intervention group over the intervention period.

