## 2.4 Null hypotheses

**Primary null hypothesis:** There is no difference between the effects of an everyday physiotherapy training programme with eye movement training and such a training programme without eye movement training on dynamic balance in people with idiopathic Parkinson's syndrome.

**Secondary null hypotheses:** There is no difference between the effects of an everyday physiotherapy training programme with gaze movement training and such a training programme without gaze movement training on functional mobility with and without manual multi-task, static balance, walking speed, health-related quality of life, freezing of gait, fall-associated self-efficacy, depression, fall rate and eye movements during dynamic balance tasks and specific training items in individuals with Idiopathic Parkinson's Syndrome.

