## 2.5 Alternative hypotheses

**Primary alternative hypothesis:** There is a difference between the effects of an everyday physiotherapy training programme with eye movement training and such a training programme without eye movement training on dynamic balance in people with idiopathic Parkinson's syndrome.

**Secondary alternative hypotheses:** There is a difference between the effects of an everyday physiotherapy training programme with gaze movement training and such a training programme without gaze movement training on functional mobility with and without manual multi-task, static balance, walking speed, health-related quality of life, freezing of gait, fall-associated self-efficacy, depression, fall rate and eye movements during dynamic balance tasks and specific training items in individuals with Idiopathic Parkinson's Syndrome.

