### 4.3.3 Primary and secondary endpoints and survey instruments

Table 2 lists the primary and secondary endpoints of the study with the respective survey instruments selected. All assessments are used in their validated German version. The implementation and psychometric criteria of the clinical assessments are described in chapter 4.4.

**Table 2:** Primary and secondary endpoints and survey instruments

| Endpoint                                                                                  | Survey                                                                                                       | Scr | BL | Int. | PI | FU
Call |
|-------------------------------------------------------------------------------------------|--------------------------------------------------------------------------------------------------------------|-----|----|------|----|------------|
| Primary clinical endpoints                                                         |                                                                                                              |     |    |      |    |            |
| Dynamic balance                                                                           | Functional Gait Assessment (FGA)                                                                             |     | X  |      | X  |            |
| Dynamic balance with eye movements (saccade speed, amplitude, latency, fixation duration) | Items 5, 6 and 10 of the Functional Gait Assessment (FGA) with mobile eye tracking using Tobii Pro Glasses 3 |     | X  |      | X  |            |
| Secondary clinical endpoints                                                       |                                                                                                              |     |    |      |    |            |
| Cognitive function                                                                        | Mini-Mental State Test (MMST)                                                                                | X   |    |      |    |            |
| Functional mobility                                                                       | Timed-Up-and-Go (TUG)                                                                                        |     | X  |      | X  |            |

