#### **4.4.4 Timed-Up-and-Go (TUG)**

The Timed-Up-and-Go is used to assess functional mobility, which is a primary endpoint of this study. (Podsiadlo and Richardson, 1991). The TUG is used as an indicator of the risk of falling during everyday movement tasks. The performance of the activities transfer from sitting to standing, walking, as well as making a turn in space, going back to the chair and sitting down is tested. For locomotion in everyday life and for the reduction of the risk of falling, the abilities to transfer from sitting to standing and to make a turn in space are of decisive importance. (Cheng et al., 1998; Mong et al., 2010)..

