## 5.6 Data analysis

### 5.6.1 Statistical data analysis

Statistical data analysis is performed using IBM SPSS software, version 26.0 (IBM Corporation, Armonk, NY, USA) and Tobii Pro Lab Analyser (Tobii, Danderyd, Sweden). The statistical significance level is defined by a p-value of  $<0.05$ . An attempt is made to avoid missing data by inspecting the questionnaires after completion and, in case of unanswered items, asking the study participants to complete them. The number of missing data is noted; due to the less sensitive topic of the study, it is assumed that missing variable values can be assigned to "missing completely at random" or "missing at random". An intention-to-treat analysis is performed for all cases analysed in their originally assigned group.

Descriptive statistics are used for demographic data and primary and secondary outcomes. Counted and nominal scaled data (gender, fall rate, recruitment, retention and adherence rate, number of missing data if applicable, number of adverse events) are reported as whole numbers or percentages. Ordinal scaled variables (MMSE, UPDRS, H & Y, FGA, BBS, PDQ-39, FOGQ, FES-I, BDI-II) are expressed as median (minimum, maximum or interquartile range) and metric variables (TUG, TUGman, FSST, 10MWT, eye movements: Saccade velocity, amplitude, latency, fixation duration) by mean (95% confidence interval, CI or standard deviation, SD). The data is also presented graphically (e.g. by bar charts, box plot or line graphs).

The eligibility rate (%) is the percentage of patients suitable for the study after applying the inclusion and exclusion criteria from the Parkinson's patients treated at the Reha Zentrum Münster during the study period.

The recruitment rate (%) is determined as follows:  $(N_{\text{Consent}}/N_{\text{eligible}}) \times 100$ ; where  $N_{\text{Consent}}$  is the number of participants who signed the informed consent form;  $N_{\text{eligible}}$  is the number of patients eligible for the study based on the inclusion and exclusion criteria.

The retention rate (%) is calculated as follows:  $(N_{\text{completed}}/N_{\text{Total}}) \times 100$ ; where  $N_{\text{completed}}$  is the number of participants who completed the study;  $N_{\text{Total}}$  is the total number of participants in the study.

Adherence rate (%) is determined as follows: (Actual number of exercise sessions/planned number of training sessions)\*100 (Osterberg & Blaschke, 2005).

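### The primary endpoint is labelled in three conflicting ways, so the result reported as primary and used to size the later trial could be chosen after the data are seen

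*Protocol*

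**What the plan says.** The Study synopsis has two entries under primary endpoints. The first is "1.1 Dynamic balance measured by the Functional Gait Assessment (FGA"). The second is "Items 5, 6 and 10 of the FGA are additionally performed with eye-tracking glasses", giving saccade velocity, amplitude, latency and fixation duration. Table 2 in section 4.3.3 also has two rows under its primary heading: the FGA, and "Dynamic balance with eye movements (saccade speed, amplitude, latency, fixation duration").

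Section 2.3 gives one primary objective: "Assessment of the effects on dynamic balance (primary endpoint"). Sections 2.4 and 2.5 frame the primary hypotheses on dynamic balance without naming an instrument, and their secondary hypotheses include "fall rate and eye movements during dynamic balance tasks and specific training items".

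Section 4.4.4 states: "The Timed-Up-and-Go is used to assess functional mobility, which is a primary endpoint of this study".

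On testing, section 5.6.1 says "The statistical significance level is defined by a p-value of" less than 0.05. The alternative hypothesis has no direction ("There is a difference between the effects of an everyday physiotherapy training programme with eye movement training" and without it), so tests are read as two-sided. The Bonferroni correction in 5.6.1 covers pairwise comparisons that follow a significant ANOVA, not the set of endpoints. The same section calls the inferential analysis preliminary and uses the between-group differences to plan a larger trial.

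**The concern.** The same eye-movement measures are primary in two places and secondary in two others, and the TUG is primary in one place and secondary in the rest. This is a contradiction within the protocol, not a detail that could be left to an analysis plan. The FGA, an eye parameter or the TUG could each be presented as the primary result with protocol text in support. The listed primaries are also analysed differently: the FGA is treated as ordinal (Mann-Whitney U test on the change), the eye parameters as metric (2 x 2 ANOVA). Nothing says which one decides.

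Two things are at stake: which outcome is registered and reported as primary, and which between-group difference is carried into the sample size of the later trial.

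A separate defect sits in the same sentences. The secondary hypotheses posit a between-group difference in eye movements during specific training items, yet objective 4 and Table 2 describe those recordings for group 1 only.

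**Working it through.** **Labels side by side**

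| Place in the protocol | FGA / dynamic balance | Eye movements on FGA items 5, 6, 10 | TUG / functional mobility |
|---|---|---|---|
| Synopsis endpoint lists | primary (1.1) | primary (1.2) | secondary (2.1) |
| 2.3 Objectives | primary | not named in objective 1 | secondary |
| 2.4 and 2.5 Hypotheses | primary (no instrument named) | secondary | secondary |
| 4.3.3 Table 2 | primary | primary | secondary |
| 4.4.4 | – | – | primary |
| 5.7.2.2 | the primary endpoint, in the singular | | |

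Table 2 also gives the label dynamic balance to the FSST, as a secondary endpoint. The primary hypothesis therefore does not fix the instrument by itself.

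**The plan's own figure**

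The protocol states no error rate across endpoints. Its only related figure is the sample size in 4.1.2.3: 30/(1 − 0.10) = 33.3, rounded up to 34. This reproduces. It also gives the 15 per group used in the simulation below (30 analysed, 1:1).

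**Chance of at least one false-positive primary result**

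Inputs: 0.05 per test, two-sided (5.6.1, 2.5). Assumption not in the protocol: any one significant listed primary would count. With k independent tests the chance is 1 − 0.95^k.

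- FGA alone, k = 1: 5.0%
- FGA + TUG, k = 2: 1 − 0.95² = 9.75%
- FGA + four eye parameters, k = 5: 1 − 0.95⁵ = 22.6%
- The same + TUG, k = 6: 26.5%
- FGA + 12 eye tests (4 parameters x 3 items), k = 13: 48.7%
- The same + TUG, k = 14: 51.2%

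Independence is unrealistic for measures taken in the same patients. A simulation of two-sample t tests (15 per group, common pairwise correlation, 20,000 runs) gave:

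| Tests | corr. 0 | 0.3 | 0.5 | 0.7 | 0.9 |
|---|---|---|---|---|---|
| 5 | 22.4% | 20.9% | 19.0% | 15.2% | 10.2% |
| 13 | 48.4% | 42.1% | 34.0% | 24.6% | 14.3% |
| 14 | 50.9% | 44.2% | 36.0% | 25.3% | 14.4% |

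The t test stands in for the Mann-Whitney test of the FGA. For the eye parameters it matches the group-by-time term of a 2 x 2 ANOVA, which with two time points is a t test on change.

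**Which count fits the text**

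Section 5.6.1 lists the eye movements as four metric variables, and Table 2 gives them one row. Five tests is the reading closest to the document, hence about 10–23%.

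**Training-item hypothesis**

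Objective 4 and Table 2 place the weekly recordings in the intervention group. Synopsis item 2.11 and sections 4.3.3.1.1 and 4.4.15 describe them without naming a group. No section states that controls are recorded during training. Exercise 4, one of the recorded exercises, is head flexion and extension in the intervention manual but an arm diagonal in the control manual, so that item would not be like for like even if controls were recorded.

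**The case against.** The strongest reply is that the intended primary can be worked out. Objective 1 and the primary hypotheses name dynamic balance, the synopsis and Table 2 tie primary dynamic balance to the FGA, and the BBS and FSST are explicitly secondary. The synopsis says eye movements are to be explored, and 5.7.2.2 speaks of one primary endpoint. The TUG sentence looks like an isolated slip in a section on measurement properties. This stands in part: an FGA-only reading is available, but it has to be inferred against two lists that say otherwise.

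A second reply is that a familywise error rate is the wrong yardstick. The trial is a pilot, its size comes from pilot rules of thumb (4.1.2.3), the criteria in 4.4.14.1 concern recruitment, retention, adherence, safety and acceptance, and no efficacy success rule is defined. This largely stands. A rule for multiplicity could also sit in an analysis plan that is not at hand, so its absence does not carry the point; the conflicting labels do.

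A reader might infer from the synopsis that the primary error rate is about 50%. The documents do not support that as the size of the problem. It needs every eye parameter tested separately on each of three items, independence between all tests, and a rule that any one significant result suffices. The protocol states none of these. A reader might also infer that controls certainly have no eye data from training. Two places limit the recordings to group 1, but others name no group, so the text calls for reconciliation.

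**Conclusion.** The point holds as a labelling contradiction. The eye-movement measures on the FGA items are both primary and secondary, and the TUG is called primary once against its secondary status elsewhere. The error rate depends on which reading is adopted: 5% for the FGA alone and about 10–23% for the FGA plus four eye parameters, assuming 0.05 per test, success on any one, and correlation from 0.9 to zero. About 50% is only an extreme scenario.

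Because inference is preliminary, these figures matter less than the freedom they illustrate: the endpoint reported as primary, and the difference used to size the later trial, could be settled after the results are known. The training-item hypothesis is a real but separate inconsistency among the secondary endpoints.

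**What to change.** 1. State everywhere, including the primary hypotheses in 2.4 and 2.5, that the single primary endpoint is the change in FGA total score from baseline to post-intervention. This matches 5.6.1, which analyses the post-minus-baseline difference for ordinal variables; naming the post-intervention score alone would create a new conflict.
2. Move the eye-tracking measures on FGA items 5, 6 and 10 to secondary or exploratory in the synopsis and Table 2.
3. Change 4.4.4 so that functional mobility (TUG) is a secondary endpoint.
4. Separately, reconcile 2.4 and 2.5 with objective 4 and Table 2 on eye movements during training items, and make synopsis item 2.11, 4.3.3.1.1 and 4.4.15 name the group recorded. If recording stays in group 1 only, remove that clause from the between-group hypotheses and describe the weekly recordings as a within-group series.

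With step 1 in place the primary error rate is 5%. The cost is protocol wording, best settled before the registration that 3.4 places after the ethics vote. No visit, measurement or sample size changes. The downside is that eye movements lose their primary label.
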